##### Patient interview guide

3.5.1.5

The guide for the semi‐structured patient interviews starts with an introductory question on their overall satisfaction with nursing care. Further questions address patients’ main nursing care needs, their experiences of nurses’ interest in and skills regarding their needs, received nursing interventions, the patients’ main aims/expected outcomes and their inclusion into nursing care planning. Patients will address the care needs that they are able to recognize. The interview notes will be recorded by hand by the interviewing APN, and all participating APNs have been previously trained in data collection and in the use of the guide(s).

##### Quality of diagnoses, interventions and outcomes (Q‐DIO)

3.5.1.6

The Q‐DIO instrument is revised for this study to assess the quality of the Advanced Nursing Process using record audits (Müller‐Staub, Lunney, et al., 2008; Müller‐Staub et al., 2009, 2010). The Q‐DIO contains a three‐point scale (0–2) for the 12 nursing assessment items and a five‐point scale (0–4) for the other three sub‐concepts (nursing diagnoses, interventions and outcomes). The higher the point total, the higher the quality of the Advanced Nursing Process. The original Q‐DIO has been validated in several studies and shows favourable validity and reliability; the internal consistency as measured by Cronbach's alpha for each sub‐concept ranged from 0.83–0.99, the test–retest reliability as measured by kappa was 0.95, and the inter‐rater reliability as measured by Fleiss’ kappa was 0.94 (Linch, Müller‐Staub, Moraes, Azzolin, & Rabelo, 2012; Linch et al., 2015; Müller‐Staub, Lunney, et al., 2008; Müller‐Staub et al., 2009, 2010). All nursing records will be evaluated by each Q‐DIO item and recorded in an SPSS data mask (SPSS Inc.). To ensure a consistent approach of its application, memos will be written, and the instrument developer is consulted.

##### Tool for demographic and organizational data

3.5.1.7

To control for influencing factors, all participating nurses will be asked about their gender, highest education grade, years of practical experience and previous seminars on the nursing process. To control for system influences, the number of beds, capacity, patients’ length of stay, nurse–patient ratio, grade and skill mix, staff turnover and organizational system characteristics will be collected from each ward by the principal investigator using standardized data collection forms.

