#### Registered nurses

3.2.1

All RNs of the six included wards will be recruited (*N = *92) for attitude measurements. Using stratified convenience sampling, a third (*N = *34) of the RNs will participate as experimental group in GCR training (*N = *17) or as control group (*N = *17). Both groups should contain a similar grade‐skill mix of ward managers, nurse instructors, Advanced Nursing Process mentors and regular RNs. All ward managers will be included. The aim is to empower them for taking responsibility on the Advanced Nursing Process. As role models, their knowledge, attitude and behaviour should spread to their teams. The inclusion criteria are being in a leadership, teaching or clinical position, applying the Advanced Nursing Process and understanding the main national language.

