##### Knowledge test

3.5.1.1

A knowledge test will be distributed to the experimental and control groups on the first and last GCR days. This test was previously developed for evaluating similar GCR training sessions. After minor adjustments and a pre‐test, it contains eleven items: six qualitative knowledge questions, two supplementary control questions on content not covered by the GCR sessions and three self‐evaluations on the learning success. For the knowledge items, the maximum attainable test score is 58 points, and for the control items, the maximum score is thirteen points. Participants take the test silently by hand under expert supervision. A maximum of 30 min is allowed for its completion and the participants fill in a personal four‐digit number (e.g. the last digits of their mobile phone) to code the test(s), thus allowing anonymous, matched comparisons before and after the GCR training.

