### Data analyses

3.6

The knowledge test and nurses’ attitude (PND scale) will be analysed using descriptive and inductive statistics. Single‐item and total scores will be compared between the two measurement points (Wilcoxon signed‐rank test) and between the experimental and control groups (Mann–Whitney *U* tests). The scores of supplementary control items for the knowledge test will be separately analysed and compared between the two measurement points and the two groups. The results of the three nurses’ attitude measurements (*t*0_2_, *t*1 and *t*2) will be evaluated using Friedman tests (Bortz & Schuster, 2016; Clauß, Finze, & Partzsch, 2011). The free‐text item answers in the knowledge test will be analysed using Mayring's (2010) seven‐step content analyses.

Participant satisfaction will be descriptively analysed based on absolute and relative frequencies and distributions. Content analyses (Mayring, 2010) will be applied to the interview with the nursing director and to the free‐text data from the satisfaction surveys.

The Q‐DIO R scores will be summed for each sub‐concept. If the data are normally distributed, unpaired *t*‐tests are applied to compare pre‐ and postintervention scores and to compare the experimental and control groups. The frequencies and patterns (variety) of the NANDA‐I nursing diagnoses will be compared between the two measurement time points and between the experimental and control groups.

Correlations among nurses’ knowledge, attitude, Q‐DIO R scores, demographic and organizational characteristics will be analysed depending on level of data and testing requirements by Pearson product–moment correlations, Spearman correlations or chi‐squared tests. All tests will be evaluated one‐sided (levels of significance 0.05) using IBM SPSS Statistics 24 (SPSS Inc.).

The qualitative evaluation of nurses’ clinical behaviour will be performed by within‐ and cross‐case analyses (Kuckartz, 2016). Qualitative observations, interviews and nursing records will be analysed using the first and second coding cycles (Saldaña, 2015). Decoding (open) is applied in the first cycle, and encoding (deductive) is applied in the second cycle. For the qualitative data analyses, MAXQDA 12 software (VERBI GmbH, 2015) will be used.

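### Role is the balancing factor for the 17 v 17 nurses but is not recorded against the anonymous code, so the comparison can be neither stratified by it nor adjusted for it

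*Protocol article*

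**What the plan says.** All references are to the protocol article.

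- **Registered nurses (3.2.1).** The nurses for the training comparison are chosen as follows: "Using stratified convenience sampling, a third" (34 nurses) "of the RNs will participate as experimental group in GCR training" or as controls, 17 in each group. Both groups should have a similar "mix of ward managers, nurse instructors, Advanced Nursing Process mentors and regular RNs". On managers the section adds: "All ward managers will be included". Role is the only characteristic named for balance between the two groups.
- **Tool for demographic and organizational data (3.5.1.7).** The nurse-level items, collected so that their influence can be controlled, are given in one sentence: "all participating nurses will be asked about their gender, highest education grade, years of practical experience and previous seminars on the nursing process". Role is not listed. Staffing structure is recorded at ward level only: "grade and skill mix, staff turnover and organizational system characteristics will be collected from each ward by the principal investigator".
- **Knowledge test (3.5.1.1).** Each nurse writes a self-chosen four-digit number on the form, "thus allowing anonymous, matched comparisons before and after the GCR training". The sections on the PND scale and the satisfaction survey use the same number. No link from the number to identity or role is described.
- **Data analyses (3.6).** Knowledge and attitude scores are compared between the two measurement points "and between the experimental and control groups (Mann–Whitney *U* tests"). Demographic and organizational data enter only through correlations.

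**The concern.** Four provisions, each reasonable alone, do not fit together. The sample is built on role, role is not listed for collection, the forms are coded so that it cannot be attached afterwards without breaking anonymity, and the test takes no account of it. A later analysis plan could change the test, but it could not recover a variable that was never tied to the scores.

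This matters because the 34 nurses are chosen by convenience within wards, so chance does not balance the individuals. The role mix is the main stated safeguard at nurse level. Managers, instructors and process mentors can be expected to know more about the nursing process than other nurses, and the article itself treats managers as role models for their teams. Knowledge and attitude are primary outcomes and carry the first hypothesis. With 17 per arm, lost precision or a small imbalance counts for more than in a large trial.

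**Working it through.** **The plan's own figures.** The only sample-size calculation is for nursing records (3.2.2). It reproduces: at one-sided 0.05, effect sizes of 0.63, 0.53 and 0.47 with power 80%, 80% and 70% need 31.9, 44.7 and 43.3 records per group by the exact t calculation, that is 32, 45 and 44 as stated. No calculation is given for the 17 v 17 nurses, and this point does not depend on the record figures.

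**Inputs.** From the article: 17 per arm, one-sided 0.05. Assumed, because the article gives no role effect: role in two levels (manager, instructor or mentor v regular nurse), explaining 10–20% of score variance; a gap of 0.5–1 SD between levels for the bias calculation; nurses treated as independent; normal approximation.

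**1. Precision.** With share of variance explained R², the standard error is multiplied by √(1 − R²), and the equivalent unadjusted size is 17/(1 − R²).

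| R² | √(1 − R²) | Cut in SE | Equivalent n per arm |
|---|---|---|---|
| 0.10 | 0.949 | 5% | 17/0.9 = 18.9, about 19 |
| 0.20 | 0.894 | 11% | 17/0.8 = 21.3, about 21 |

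The difference detectable with 80% power, (1.645 + 0.842) × √(2/17) = 0.85 SD, falls to 0.81 SD (R² = 0.10) or 0.76 SD (R² = 0.20).

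**2. What a two-level role can explain.** With a share p of senior nurses and a gap d in total-SD units, R² = p(1 − p)d².

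- At d = 1 the maximum, at p = 0.5, is 0.25. If the SD is the within-role SD, it is 0.25/1.25 = 0.20.
- With 3 seniors in 17 and d = 1: (3/17)(14/17) = 0.15.
- At d = 0.5 the maximum is 0.25 × 0.25 = 0.06, a cut in the standard error of only 3% (√0.94 = 0.97).

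So 10–20% presumes a fairly large gap between roles.

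**3. Bias if the analysed forms are unbalanced.** With k more seniors in one arm, bias = (k/17) × d. If the excess is in the trained arm, the one-sided type I error is 1 − Φ(1.645 − bias/√(2/17)).

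| Extra seniors | Bias, d = 0.5 to 1 | Type I error (nominal 0.05) |
|---|---|---|
| 1 | 0.03–0.06 SD | 0.059–0.070 |
| 2 | 0.06–0.12 SD | 0.070–0.096 |
| 3 | 0.09–0.18 SD | 0.083–0.129 |

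An excess in the control arm would hide an effect instead.

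**4. If the mix is exactly balanced.** The unadjusted test is then conservative, not biased. Its true one-sided size is 1 − Φ(1.645/√(1 − R²)): 0.042 at R² = 0.10 and 0.033 at R² = 0.20.

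**The case against.** - **Recruiters know the roles.** Nurses cannot be selected by role unless the team knows each one's role, so counts per arm at enrolment can be tabulated without the forms. This stands. A reader might infer that the role mix cannot be checked at all; the article does not support that. What cannot be checked is the mix among the forms analysed, after non-response or unmatched codes.
- **There are partial substitutes.** Both groups take the knowledge test and the PND at baseline, linked by code, and education, experience and previous seminars are asked of each nurse. A role imbalance that matters should show in part there. This also stands, but none of these items identifies a manager, instructor or mentor.
- **Balance by design still protects the comparison.** Correct. It would be wrong to say that the stratification is wasted: a balanced mix guards against role bias even when the test ignores role. The loss is then precision.
- **The article condenses a fuller protocol.** The choice of test could fairly be left to an analysis plan. But the article states the nurse-level items as a closed list and describes the anonymous coding, and those two together remove the option.
- **Ward.** A reader might go further and infer that the trainees will be spread unevenly over the three wards. The article does not list the strata, so this is conjecture. All nurses on the experimental wards are also meant to join case meetings there, so record quality would not hang on the trainees' location alone.

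**Conclusion.** The point holds as a cheap improvement, not as a flaw that invalidates the comparison. As written, role cannot be tied to an individual score, so the 17 v 17 knowledge and PND comparisons cannot use the one factor on which the sample was built.

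The main cost is a standard error about 5–11% larger than it need be, if a two-level role explains 10–20% of score variance; with a role gap of only 0.5 SD the loss is at most about 3%. The secondary cost is a possible shift of 0.03–0.18 SD if 1–3 more senior nurses remain in one arm. The upper end needs both an imbalance of three and a 1 SD gap, and the sampling aims to prevent that imbalance.

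A reader might assume that role explains 40% of the variance, equal to 17/0.6 = 28 nurses per arm. That does not fit a two-level role with a 1 SD gap, which explains at most about 20–25%. All sizes rest on assumed role effects.

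**What to change.** 1. Add one item to the coded nurse form: manager, instructor or mentor v regular nurse.
2. Report the role mix by arm twice: at recruitment, and for the code-matched forms analysed.
3. Compare knowledge and PND scores in the 17 v 17 with a role-stratified rank test (van Elteren), or with role as a covariate.

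The article says that data collection has started. If the baseline forms are already in, the item can go on a later form and ask for the role held at the start of the study; the code carries it back to the earlier scores.

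The cost is one tick box and one sentence of analysis. The downside is slightly less anonymity, which two broad levels keep small. Ward should not be added: with so few senior nurses on each ward, the combination could identify individuals.

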#### Measurement time points before and after the GCR study intervention

3.5.2

Data collection will occur at three time points; the flow chart in Figure 3 presents all data collection methods and time points. As baseline measurement before the GCR intervention (*t*0_1_ + *t*0_2, _illustrated in boxes): a sample of nursing records will be drawn, and nurses of the intervention and control group perform the knowledge tests and all nurses of the participating wards fill out the PND scales (illustrated in circles). After GCR, the participants complete knowledge tests and PNDs for the second time and complete the satisfaction survey (*t*1). After ending of the GCR intervention, all nurses complete the PND a second and a third time. At that time, a second sample of nursing records will be drawn. In addition, patient care will be observed (nurses’ clinical performance) and patients are interviewed to cross‐validate the Q‐DIO R results on the quality of the Advanced Nursing Process as described in the nursing records.

**Figure 3 nop2299-fig-0003:**
[figure not shown]
Flow chart of the study schedule. D_1 _‐ D_4_ = Days 1–4 of guided clinical reasoning training days; GCR = GCR case meetings on the wards; *t*0_1_ + *t*0_2_ = baseline

### Data analyses

3.6

The knowledge test and nurses’ attitude (PND scale) will be analysed using descriptive and inductive statistics. Single‐item and total scores will be compared between the two measurement points (Wilcoxon signed‐rank test) and between the experimental and control groups (Mann–Whitney *U* tests). The scores of supplementary control items for the knowledge test will be separately analysed and compared between the two measurement points and the two groups. The results of the three nurses’ attitude measurements (*t*0_2_, *t*1 and *t*2) will be evaluated using Friedman tests (Bortz & Schuster, 2016; Clauß, Finze, & Partzsch, 2011). The free‐text item answers in the knowledge test will be analysed using Mayring's (2010) seven‐step content analyses.

Participant satisfaction will be descriptively analysed based on absolute and relative frequencies and distributions. Content analyses (Mayring, 2010) will be applied to the interview with the nursing director and to the free‐text data from the satisfaction surveys.

The Q‐DIO R scores will be summed for each sub‐concept. If the data are normally distributed, unpaired *t*‐tests are applied to compare pre‐ and postintervention scores and to compare the experimental and control groups. The frequencies and patterns (variety) of the NANDA‐I nursing diagnoses will be compared between the two measurement time points and between the experimental and control groups.

Correlations among nurses’ knowledge, attitude, Q‐DIO R scores, demographic and organizational characteristics will be analysed depending on level of data and testing requirements by Pearson product–moment correlations, Spearman correlations or chi‐squared tests. All tests will be evaluated one‐sided (levels of significance 0.05) using IBM SPSS Statistics 24 (SPSS Inc.).

The qualitative evaluation of nurses’ clinical behaviour will be performed by within‐ and cross‐case analyses (Kuckartz, 2016). Qualitative observations, interviews and nursing records will be analysed using the first and second coding cycles (Saldaña, 2015). Decoding (open) is applied in the first cycle, and encoding (deductive) is applied in the second cycle. For the qualitative data analyses, MAXQDA 12 software (VERBI GmbH, 2015) will be used.

Data and method triangulation will take place by applying Kirkpatrick's four levels. First, the findings of participants’ satisfaction survey and directors’ interview will be compared to verify whether these sources are mutually supportive (Reaction). Second, a data synthesis of findings from observations, patient interviews and nursing records (within‐ and cross‐case analyses) will be performed to evaluate nurses’ clinical performance of the Advanced Nursing Process (Behaviour). Finally, the chain of evidence (according to Kirkpatrick) will be verified as follows: a positive lower level is prerequisite for the next higher level; for example, a positive knowledge test (Learning) is a prerequisite for positive clinical performance (Behaviour).

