#### Nursing records

3.2.2

By using a web‐based random generator, a sample of nursing records (*N = *180) will be drawn (https://www.random.org/). Nursing records covering at least 4 days and at least one nursing diagnosis will be selected from all six wards (experimental group *N = *90, control group *N = *90). The sample‐size calculation was performed using *t*‐tests for unpaired samples (one‐sided) and bases on previous results for using the Q‐DIO for all three sub‐concepts of the instrument (nursing diagnoses, interventions and outcomes) (Müller‐Staub, Needham, et al., 2008). An effect size of 0.5 (mean) on a scale from 0–4 is assumed. For nursing diagnoses, 32 nursing records per group are required; we assumed an effect size of 0.63 (power 80%). For nursing interventions, 45 records (effect size, 0.53; power, 80%) are required and for nursing outcomes, 44 records (effect size, 0.47; power, 70%) are required. To ensure an even distribution in the experimental and control groups, 15 nursing records will be selected per ward (*N = *45 records before and 45 records after the study intervention, totalling *N = *90) for each group (Bortz & Schuster, 2016).

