##### Positions on the Nursing Diagnoses Scale (PND)

3.5.1.2

The nurses’ attitude towards nursing diagnoses will be measured using the self‐assessment instrument PND (Lunney & Krenz, 1994), which contains 20 items with positive and negative pairs of bipolar attitude adjectives on a 7‐point Likert scale. The total score ranges from 20–140; the more positive the attitude, the higher the total score. The German PND version has been previously evaluated (Leoni‐Scheiber, Gothe, & Müller‐Staub, 2016). The psychometric properties of the original PND showed favourable results: its content validity exceeded an agreement of 90% by four expert raters (Lunney & Krenz, 1994), the test–retest reliability as measured by intraclass correlation coefficient was 0.90 (95% CI [0.87, 0.92]), and the internal consistency as measured by Cronbach's alpha coefficient was 0.96 (Romero‐Sánchez, Paloma‐Castro, et al., 2013). The construct validity was measured by confirmatory factor analysis and showed highly correlated factors in the three‐factor model solution (≥0.96) (D'Agostino et al., 2016). The PND requires 5 min to complete and will be filled out by the participating nurses in handwriting on the first and last GCR days and 3 months later on their respective wards. To assure anonymity and to ensure that the results can be compared with the knowledge tests of each nurse, the participants will be asked to fill in the same four‐digit number as in the other instrument.

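### Knowledge and attitude baselines are linked nurse by nurse in both arms, but no planned test uses them to adjust the arm comparison that hypothesis 1 asks for

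*Protocol article*

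**What the plan says.** All references are to the protocol article.

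- **Hypotheses.** Hypothesis 1 (knowledge and PND) and hypothesis 3 (Q-DIO R) both state that the experimental arm will score higher than the control arm after the training.
- **Baselines.** The section on measurement time points schedules baseline records, knowledge tests in both arms, and PND forms from all nurses on the six wards. The Knowledge test section introduces a personal four-digit code, "thus allowing anonymous, matched comparisons before and after the GCR training". The PND section asks for the same number.
- **Knowledge and PND tests.** Under Data analyses, "total scores will be compared between the two measurement points" with the Wilcoxon signed-rank test, and between arms with the Mann–Whitney U test. The three PND measurements go to Friedman tests.
- **Q-DIO R tests.** If the data are normally distributed, unpaired t-tests are used to compare pre- and "postintervention scores and to compare the experimental and control groups".
- **Error rate.** "All tests will be evaluated one‐sided", with "levels of significance 0.05".

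No change-score comparison, covariance analysis, arm-by-time term or difference in differences is named. Demographic and organizational factors are collected so that influences can be controlled, but they enter only correlations or chi-squared tests.

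**The concern.** The plan answers two questions separately: did scores move within an arm, and do the arms differ? It does not join them in one estimate of the arm difference at follow-up given where each nurse started. Three things are at stake.

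1. **Baseline imbalance.** Three wards per arm are randomised from a mix of geriatric, medical and surgical wards, and the 34 nurses in the training and control groups are a stratified convenience sample. Chance or selection differences at baseline are likely, and an unadjusted contrast carries them into the result.
2. **Misreading.** With separate pre–post tests and no stated rule, significance in the experimental arm but not in the control arm can be taken for an effect.
3. **Precision.** With 17 nurses per arm, the linked baseline is the cheapest precision available, and it goes unused in the arm comparison.

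**Working it through.** **The plan's own figures.** The only sample size calculation concerns records: an unpaired, one-sided t-test. For diagnoses, "we assumed an effect size of 0.63 (power 80"%) gives 32 per group; for interventions, "45 records (effect size, 0.53; power, 80"%); for outcomes, 44 records at 0.47 and 70% power. The exact one-sided t calculation gives 31.9, 44.7 and 43.3, which round up to the stated 32, 45 and 44. The record sample was therefore sized for an unadjusted two-group contrast.

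**Knowledge, 17 v 17.** Inputs: 17 per arm (Registered nurses section) and one-sided 5% (Data analyses). The 80% power is borrowed from the record calculation, and the baseline–follow-up correlation r is an assumption.

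- Unadjusted, by the t distribution, the detectable difference is 0.871 SD.
- Covariance adjustment multiplies the error variance by 1 − r².
- r = 0.5: 1 − 0.25 = 0.75, and 0.871 × √0.75 = 0.75 SD.
- r = 0.7: 1 − 0.49 = 0.51, and 0.871 × √0.51 = 0.62 SD.

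Ward clustering is ignored throughout, and the t-test stands in for the Mann–Whitney test.

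**Imbalance.** A baseline difference of 0.3 SD (assumed) shifts the expected unadjusted follow-up contrast by 0.3 × r: 0.15 SD at r = 0.5 and 0.21 SD at r = 0.7.

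**Separate within-arm tests.** Suppose both arms truly change by the same amount and each pre–post test has power p, independently. The pattern of experimental significant and control not significant then has probability p(1 − p): 0.16 at p = 0.2 or 0.8, and 0.25 at p = 0.5. There is no arm difference in any of these cases.

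**Q-DIO R.** Each arm has 15 × 3 = 45 records before and 45 different records after. The stated effect sizes are read as the arm difference in SD units; clustering is ignored and the normal approximation used. Power is Φ(d/SE − 1.645).

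| Sub-concept | d | Post-only, SE = √(2/45) = 0.211 | Arm-by-period, SE = √(4/45) = 0.298 |
|---|---|---|---|
| Diagnoses | 0.63 | 91% | 68% |
| Interventions | 0.53 | 81% | 55% |
| Outcomes | 0.47 | 72% | 47% |

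Keeping the stated 80/80/70% power for the arm-by-period contrast needs n = 4[(1.645 + z)/d]² records per cell: 63, 89 and 86.

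**Ward-mean covariate for Q-DIO R.** I simulated six ward means per period, 15 records each, with d = 0.53 and one-sided 5%. The ICC and the correlation of ward effects between periods are assumptions. At ICC 0.10, post-only power is 38%. Adjusted for the ward baseline mean, it is about 41%, 37% and 32% at between-period correlations of 1.0, 0.8 and 0.5. At ICC 0.05, adjustment lowers power at all three correlations (48% to 43%, 41% and 39%). At ICC 0.20, power goes from 28% to 42%, 31% and 25%. The covariate leaves three degrees of freedom, so it may gain or lose.

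**The case against.** The strongest reply is that an unadjusted contrast is not invalid. Wards are allocated at random, the hypotheses ask whether arms differ after the training, and the Mann–Whitney test answers that. This stands as far as ward allocation goes: the loss is then mainly of precision and of protection against imbalance. It is weaker for the 34 knowledge-test nurses, who are a convenience sample within wards. Nor is this a detail left to a fuller plan, because the article names its tests.

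Several stronger readings are tempting, and the document does not support them:

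- **That every main outcome has an unused baseline.** Satisfaction is listed as primary but is collected only on the last training day.
- **That baselines never enter an arm comparison.** The time point of the between-arm tests is not stated, so a comparison at baseline is possible. It would still adjust nothing.
- **That PND error variance would fall by 81%.** Test–retest reliability "as measured by intraclass correlation coefficient was 0.90 (95% CI [0.87, 0.92"]), and 0.90² = 0.81. That figure describes the scale's repeatability, not the correlation across a five-month training period. The 17 v 17 figures do not describe PND either, which is sought from all 92 nurses.
- **That the Friedman test is the wrong test of hypothesis 1.** The plan does not assign it to that hypothesis.
- **That ward-level chance differences measure this loss.** At an assumed ICC of 0.10 their SD is √(2 × 0.10/3) = 0.26. That is a clustering effect, whose remedy is a ward term.
- **That adjusting Q-DIO R is equally free.** Its records are not linked, and the power figures above show the price.

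**Conclusion.** The point holds for knowledge and PND. The article fixes within-arm tests and unadjusted between-arm tests, and never uses individually linked baselines to adjust the comparison in hypothesis 1. For knowledge, the detectable difference would fall from 0.87 SD to about 0.75 or 0.62 SD, subject to the assumed correlations of 0.5 and 0.7 and with clustering ignored. No figure is offered for PND, because the document gives no baseline–follow-up correlation.

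For Q-DIO R, it is also true that the baseline period does not adjust the arm contrast, but this is a trade-off and not an omission that can be repaired for nothing. The planned arm comparison should be changed for the first two outcomes and supplemented for the third.

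**What to change.** 1. **Knowledge.** Make the primary analysis one between-arm estimate, with confidence interval, of the follow-up score adjusted for the nurse's own baseline (ANCOVA, or rank-based if the distribution requires it).
2. **PND.** Use a baseline-adjusted repeated-measures model with an arm-by-time term for the follow-up occasions.
3. **Ward.** Account for ward in both, and acknowledge that six wards leave few degrees of freedom.
4. **Within-arm tests.** Keep the Wilcoxon and Friedman tests as description. State that no effect will be inferred from significance in one arm and not in the other.
5. **Q-DIO R.** Add a ward-baseline or arm-by-period analysis as a sensitivity analysis, and state its lower or uncertain power.

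For knowledge and PND the cost is analysis wording only: the baselines and the linking code are already planned. Data collection has started, so the change should be recorded before the follow-up data are analysed. For Q-DIO R no extra records are needed if the analysis stays a sensitivity analysis. Making the unconstrained arm-by-period contrast primary at the stated power would take about 63, 89 and 86 records per cell instead of 45, before any allowance for clustering.
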